### Spinal manipulation intervention

A standardized side lying, HVLA-SM is the treatment procedure utilized. Participants lie in a lateral recumbent position with the lower leg straightened and the superior or free leg flexed at both the hip and knee and adducted across midline. The DC, standing and facing the participant, stabilizes the superior shoulder or upper arm with one hand (i.e. non-thrusting hand) as the participant’s forearms rest across the chest or abdomen. The participant’s free leg is stabilized by the DC’s thigh or lower leg (i.e. contacting leg, the same side as the thrusting hand). The manipulative load is delivered by a quick, and short controlled movement of the DC’s shoulder, arm, and hand in combination with a slight body drop. The areas where the thrusting hand contacts the participant include lumbo-pelvic tissues over or adjacent to vertebral mammillary and spinous processes, between and slightly lateral to the posterior superior iliac spine of the ilium, ischial tuberosity, and the sacrum. The manipulative load is also transmitted to participants through the clinician’s stabilizing thigh/leg, resulting in a twisting force directed to the pelvis. In the current study the thrust is only delivered using the palmar aspect of the hand. Other side lying HVLA-SM procedures utilizing other manual contacts, such as pulling on a lumbar spinous process with fingers, are not utilized. The HVLA-SM is delivered by a team of trained and experienced clinicians who have at least 15 years of clinical experience using HVLA-SM for treating patients with LBP. To enable the assessment of segmental load at the lumbosacral region during the TV1, TV5, and TV12, the patient’s upper body is restrained by an external strap system while the clinician places the non-thrusting hand on a rest located near the participant’s free shoulder
[50, 51].

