For Specific Aim 2, the variations in kinetic measures will be summarized using a hierarchical linear regression model with random effects for clinician and for participant nested within clinician. Intraclass correlation coefficients will be computed to establish if there is substantial consistency within clinician within participants and within clinician across participants and if there is sufficient variation between clinicians to allow evaluation of how variations in kinetic measures can predict patient-centered outcomes. If the random effect for participant within clinician is non-significant, or the intraclass correlation coefficient is 0.7 or higher, then the estimated random effect for clinician will be considered a sufficient summary of the delivery of care by an individual clinician. In this case, the association between this random effect and patient-centered outcomes will be evaluated using a linear mixed regression model. If there is not sufficient consistency within clinician between patients, but there is consistency within a clinician within participants, it will indicate that clinicians vary their care by participant but provide a consistent level of care across the course of treatment. In this case, the linear mixed regression model will be used to estimate the association between random effects specific to the clinician/participant combination and patient-centered outcomes. If consistency within clinicians and within participants cannot be established, this indicates substantial variation in the care provided across time by clinicians within a participant. In this case, we will fit a linear mixed regression model with time-varying covariates to assess the association between the kinetic measurements at a particular time point and patient-centered outcomes at the subsequent visit(s).

In the analysis for both specific aims 1 and 2, the complexity introduced by modeling with time-varying covariates may be better served with conditional linear mixed models. Regardless of what model is chosen, alternative models will be fit to assess the sensitivity of the statistical model to any assumptions about consistency.

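### The Specific Aim 2 rule reads a non-significant participant effect as consistent care, so delivery that varies from visit to visit can be collapsed to one value per clinician

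*Protocol article*

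**What the plan says.** All of this is in the protocol article, Statistical analysis, in the text on Specific Aim 2. The kinetic measures are modelled with "random effects for clinician and for participant nested within clinician", which leaves visit-to-visit variation as the residual. ICCs are to describe consistency within participants and across a clinician's participants, and to show "if there is sufficient variation between clinicians to allow evaluation of how variations in kinetic measures can predict patient-centered outcomes".

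Three branches follow:

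1. The first applies under this condition: "If the random effect for participant within clinician is non-significant, or the intraclass correlation coefficient is 0.7 or higher". One estimated effect per clinician is then taken to stand for everything that clinician delivers, and the outcome analysis uses it as the exposure: "the association between this random effect and patient-centered outcomes will be evaluated using a linear mixed regression model".
2. If delivery is not consistent across a clinician's participants but is consistent within a participant, effects specific to the clinician/participant pair are used.
3. If neither kind of consistency can be shown, "this indicates substantial variation in the care provided across time by clinicians within a participant", and a model with time-varying covariates is fitted.

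The text on Aim 2 is followed by a promise covering both aims: "alternative models will be fit to assess the sensitivity of the statistical model to any assumptions about consistency".

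**The concern.** Failing to reject a zero participant effect is not evidence that a clinician delivers consistent care. Two quite different situations produce it: care that really is uniform across a clinician's participants and visits, and care that varies so much between visits that stable participant differences cannot be seen. The first supports a single value per clinician. The second is what the third branch describes. The residual variance plays no part in the first trigger, so the rule cannot tell the two apart, and the first branch is reached before the third.

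Aim 2 exists to give preliminary estimates of whether differences in thrust contact force and segmental load relate to patient-centered outcomes. If the data go down the wrong branch, every participant of a clinician receives the same dose value, and the main estimate no longer uses the variation in delivery within clinicians.

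**Working it through.** The protocol gives no probability or power figure for this rule, so there is nothing to reproduce. The check is how often the first trigger fires when visit-to-visit variation dominates.

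**Inputs**
- Participants: 80 (Sample size).
- Kinetic visits per participant, m: 2 for contact force (TV3, TV9) and 3 for segmental load (TV1, TV5, TV12) (Patient visit protocol; Dynamic stiffness).
- Clinicians, K: not stated. The Spinal manipulation intervention section says only "The HVLA-SM is delivered by a team of trained and experienced clinicians". Range assumed: 3 to 10.
- Significance level: not stated; 0.05 assumed.
- ρ = participant variance / (participant + visit-to-visit variance), within clinician. It is not given, so a range is shown. The visit-to-visit share is 1 − ρ.

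**Formula.** The nested F test of participant within clinician has 80 − K and 80(m − 1) degrees of freedom. The expected mean-square ratio is 1 + mρ/(1 − ρ). Hence

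P(non-significant) = P(F ≤ F_crit / [1 + mρ/(1 − ρ)]).

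**Example, K = 5, ρ = 0.10**
- m = 2: F_crit(75, 80) = 1.455; ratio 1 + 0.2/0.9 = 1.222; 1.455/1.222 = 1.190; probability 0.78.
- m = 3: F_crit(75, 160) = 1.372; ratio 1 + 0.3/0.9 = 1.333; 1.372/1.333 = 1.029; probability 0.57.

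**Results, K = 5**

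| Visit-to-visit share | 2 visits | 3 visits |
|---|---|---|
| 100% | 0.95 | 0.95 |
| 95% | 0.89 | 0.81 |
| 90% | 0.78 | 0.57 |
| 80% | 0.45 | 0.12 |
| 70% | 0.14 | 0.01 |

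For K from 3 to 10, the 90% row moves only from 0.777 to 0.782 (2 visits) and from 0.562 to 0.579 (3 visits). With an assumed 60 evaluable participants and K = 4, the 90% row becomes 0.81 and 0.64.

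**Does the or matter?** A simulation (K = 4, 2,000 runs per setting) compared the rule as written with one requiring only a clinician ICC of at least 0.7. The clinician share of total variance was 0.10.

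| Participant / visit-to-visit share of total | Rule as written, 2 visits | Rule as written, 3 visits | ICC rule only |
|---|---|---|---|
| 0 / 0.90 | 95% | 94% | 0% |
| 0.05 / 0.85 | 88% | 79% | 0% |
| 0.10 / 0.80 | 74% | 52% | 0% |

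In these settings the misrouting comes wholly from the non-significance trigger.

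**What the clinician-level result then rests on.** There are K distinct dose values. The two-sided 5% critical correlation is t/√(K − 2 + t²), with t on K − 2 degrees of freedom: 0.997, 0.950, 0.811 and 0.632 for K = 3, 4, 6 and 10. With 80 participant-level values it is 0.220.

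**The case against.** The strongest reply is that the same section commits to sensitivity models aimed at exactly this consistency assumption, and to ICCs that would reveal poor consistency. Within-clinician variation would then be used somewhere, so it is not lost altogether. That stands as mitigation. But no alternative model or threshold is named that would reverse the primary choice, and the check on between-clinician variation has no cut-off and is not a condition of the rule.

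A second reply is that misrouting is common only when visit-to-visit variation dominates heavily, and no figure in the protocol says that it will. This also stands: at a 70% share the risk is small. Residual variance also includes measurement error, so a large residual is not purely erratic delivery.

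Three stronger readings are tempting, but the protocol does not support them:

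- **The 0.7 applies to the wrong ICC.** A reader might infer that it is the within-participant ICC, which could be high purely through stable participant differences. The second branch would then be largely pre-empted, so the context points to consistency within clinician across participants. What remains is a wording clarification.
- **Standard errors will be too small because 80 participants are treated as independent.** The article names a linear mixed model without listing its random effects, and an article may leave that list to the full plan. Inflated type I error follows only if a clinician term is omitted, which is not stated. Nor would a random clinician intercept remove confounding of a clinician-level exposure; that limit belongs to any observational comparison of clinicians.
- **There are only a handful of clinicians.** The number is not given. The routing fault does not depend on it, although the precision of a clinician-level result does.

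**Conclusion.** The rule is wrong as written. Its first trigger accepts a non-rejection as proof of consistency, and so captures cases that the third branch is meant to handle. The risk runs from 0.95 when within-clinician variation is entirely visit-to-visit down to 0.14 (2 visits) or 0.01 (3 visits) at a 70% share. It is greater for contact force, which has fewer kinetic visits. These figures assume a 5% level, 80 participants with complete kinetic data, and normally distributed variance components.

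Aim 2 is secondary and exploratory. The consequence is an effect-size estimate taken at the wrong level, not a false confirmatory claim. Because such estimates are what Aim 2 is meant to deliver, the rule should still be corrected.

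**What to change.** - Remove non-significance of the participant effect as a trigger.
- Name the ICC to which 0.7 applies; the context implies within clinician across participants.
- Choose the summary from the estimated clinician, participant and visit-to-visit variance components, preferably with intervals, so that the visit-to-visit share enters the decision.
- Whenever the clinician-level summary is used, also report the model with participant- and visit-level kinetic measures, with clinician as a random effect in the outcome model.
- Report any clinician-level association as descriptive, with precision based on the number of clinicians.

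The cost is analysis wording only; no data collection changes. Clinician-level results will look less precise. Participant means over few visits are also noisy when visit-to-visit variation is large: at a 90% share their reliability is mρ/(mρ + 1 − ρ), which is 0.2/1.1 = 0.18 with 2 visits and 0.3/1.2 = 0.25 with 3. The participant-level coefficient would then be attenuated and should be read with that in mind.

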#### Sample size

A minimum of 80 participants will be enrolled in the current study. The sample size should be sufficient to obtain preliminary estimates of variability and effect size through our planned data analysis, taking into consideration the possibility of dropouts and technical issues that may occur given the rigor and complexity of this study protocol.

## Discussion

The primary objective of the current study is to examine the predictive value of spinal stiffness and FRP for patient-centered outcomes in those with chronic LBP and treated with HVLA-SM. However, it also allows us to examine two domains that may contribute to the therapeutic effects of SM (i.e. neurophysiological and biomechanical processes). Analyzing both spinal stiffness and FRP measures in LBP patients undergoing SM treatment may help elucidate the contributions of passive (skeletal, ligamentous and disc structures) and active (muscles) structures during and following HVLA-SM, thus providing evidence for suspected therapeutic mechanisms
[67].We hypothesize that changes in lumbar spine stiffness may be in part attributed to material changes in spinal tissues and altered paraspinal muscle activity induced by SM. Figure 
5 illustrates two potential mechanistic pathways (biomechanical and neurophysiological) that are shared as putative mechanisms of LBP, whereby SM may lead to altered spinal stiffness and flexion-relaxation phenomenon in LBP patients. Knowledge gained from this study will further our understanding of the neuro-biomechanical mechanisms influenced by SM and may provide objective assessment measures for use in future clinical trials.

**Figure 5 Fig5:**
[figure not shown]
**Putative effects of low back pain (A) and spinal manipulation (B).**

## Abbreviations

AE: Adverse events
BL1: Baseline Visit 1
BL2: Baseline Visit 2
C1-C7: T1-T12, L1-L5, and S1-S3: Segments of cervical, thoracic, and lumbar spines, and sacrum
DC: Doctors of chiropractic
DSMC: Data and safety monitoring committee
EMG: Electromyography
FRP: Flexion-relaxation phenomenon
FRR: Flexion-relaxation ratio
GSV: Global stiffness variation
HVLA-SM: High velocity low amplitude spinal manipulation
IRB: Institution Review Board
LBP: Low back pain
NIH: National Institute of Health
NRS: Numerical rating scale
PROMIS: Patient Reported Outcomes Measurement Information System
QTF: Quebec Task Force (classification for Spinal Disorders)
RMDQ: Roland Morris Disability Questionnaire
SM: Spinal manipulation
RMS: Root-mean-square
SQL: Structured Query Language
TV: Treatment visit
VAS: Visual analog scale.
